### Ethics approval

The study has received approval from Warwickshire LREC (reference number: RE 610).

### Trial Analysis

Data will be entered in SPSS. A random 20% of the data will be entered twice to check for discrepancies with the original data. Descriptive methods will be used to demonstrate the consistency of the three groups, describe participant characteristics, to compare the refusers with the study participants and report levels of participation and drop out. Comparison of nurse and peer supporter outcome data, experiences and feedback will be provided. Analysis of variance will be used to evaluate baseline characteristics of participants compared to non-participants, overall significance of improvement across outcome measures, and dropout versus maintainers. For each patient, change in physiological measures from start to 6 months will be calculated and analysed using t-test for matched groups for both intervention and control groups. The magnitude of change in both primary and secondary outcome measures will be estimated and the 95% confidence intervals given. *Formal Statistical Input*: A research fellow in medical statistics will provide statistical support and advice throughout the study.

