### Aims of the Trial

The hypotheses to be tested in this study are that telecare motivational interviewing will be acceptable to patients and primary care health professionals; will be associated with improved social and psychological status; healthier lifestyle choices; and enhanced satisfaction with care.

We propose to:

1. Determine the impact on quality of care, behavioural change and patient responsiveness of a centralised, expert telecare (nurse and peer-led motivational support by telephone) intervention.

2. Compare the impact of nurse and peer supporter telecare provision against routine care.

3. Obtain clinical data as a means to identifying patterns and trends to be used in conjunction with behavioural change outcomes, in order to determine the value of undertaking a full scale RCT of the cost and clinical effectiveness of the intervention.

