### Experiments Proposed Including End Points

The hypotheses to be tested are that the telecare intervention compared with routine care alone will improve adherence to the change in medication targeted; improve clinical and psychological status; encourage healthier lifestyle choices and enhance satisfaction with care. In addition, that it will be acceptable to patients and primary care health professionals.

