#### Baseline Data

In addition to the questionnaires outlined below, for patients who consent to be randomised, sex, age, ethnicity, diabetes history, most recent clinical parameters (HbA1c, BP, BMI, total plasma cholesterol, HDL: total cholesterol ratio, and plasma triglycerides), prescribed medication, smoking status, phone number, access hours, and any provisos requested by the patient will be recorded on a pro forma at recruitment by practice staff. Patients who do not wish to participate in the study will be asked for consent to include their reasons for not doing so, and their sex, age, ethnicity, most recent clinical parameters and smoking status will be recorded. This will allow for comparison between the characteristics of participants and non-participants.

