#### Sample size

The sample size is based upon the primary outcome measure of self efficacy, measured using the DMSES and has been constructed to detect a difference in the primary outcomes of self efficacy perceptions and psychological adjustment. A sample of at least 300 patients (minimum 100 in each arm) has been constructed to detect a difference in self-efficacy scores with an effect size of 0.35, 80% power at a level of 5% significance level [25]. Allowing for an attrition rate of 25% from initial recruitment, we will require 125 subjects in each arm (i.e. 375 participants in total).

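### The only test named for the primary outcome is an overall ANOVA of improvement; it isolates neither comparison with routine care and is less precise than a baseline-adjusted analysis

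*Protocol article*

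**What the plan says.** - **Primary outcome.** The Sample size section says: "The sample size is based upon the primary outcome measure of self efficacy, measured using the DMSES". The design figures are "effect size of 0.35, 80% power at a level of 5% significance level", giving 100 evaluable patients per arm, raised to 125 for 25% attrition.
- **Aims.** The second aim is: "Compare the impact of nurse and peer supporter telecare provision against routine care". The section on experiments and end points words the hypothesis as "the telecare intervention compared with routine care alone will improve adherence to the change in medication targeted".
- **Analysis.** The Trial Analysis section says: "Analysis of variance will be used to evaluate baseline characteristics of participants compared to non-participants, overall significance of improvement across outcome measures". A matched t-test on the change from start to 6 months is limited to physiological measures. The section also promises the size of change in primary and secondary outcomes with 95% confidence intervals, and a nurse and peer comparison for which no method is named.
- **Baseline score.** The Baseline Data section opens "In addition to the questionnaires outlined below, for patients who consent to be randomised" and then lists the clinical items to be recorded at recruitment. This implies that DMSES is collected at baseline in every arm.

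**The concern.** DMSES is a questionnaire score, so the matched t-test does not cover it and the ANOVA of improvement is all that is left. There are two problems.

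1. **The question answered.** An overall test across three arms can show that the arms are not all alike. It does not show whether nurse support or peer support differs from routine care. The promised confidence intervals are for the size of change and are not tied to any between-arm contrast.
2. **Precision.** Improvement reads as change from baseline. In a randomised comparison, a change score uses the baseline score less efficiently than a model with baseline as covariate.

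At stake are a primary p-value that does not address the second aim directly, and power lost although the baseline score appears to be collected anyway.

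**Working it through.** **Inputs from the protocol article:** effect size 0.35; 5% significance; 80% power; 100 evaluable and 125 recruited per arm; 25% attrition. Completers: 125 × 0.75 = 93.75, taken as 94 per arm.

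**Assumed, because not stated:** two-sided test; 0.35 in SDs of the score; equal variance at baseline and 6 months; baseline to 6-month correlation r between 0.3 and 0.6.

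**Step 1. The plan's own figure** (normal approximation, z for 80% power = 0.842):
- Pairwise, one-sided 5%: n = 2(1.645 + 0.842)² / 0.35² = 101 per arm. This matches 100.
- Pooled telecare versus control (2:1), two-sided: n = 1.5(1.960 + 0.842)² / 0.35² = 97 controls. This roughly matches.
- Pairwise, two-sided: n = 2(1.960 + 0.842)² / 0.35² = 129 per arm. No match.
- Overall three-arm F test on 6-month scores (noncentral F): 119 per arm if one or both telecare arms differ by 0.35, and 159 if one arm lies midway. No match.

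The article says only that the sample "has been constructed to detect a difference in self-efficacy scores". It fixes neither the contrast nor the sidedness.

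**Step 2. Variance of each analysis**, with the score variance set to 1:
- Change score: 2(1 − r)
- ANCOVA: 1 − r²
- Ratio of ANCOVA to change score: (1 − r²) / [2(1 − r)] = (1 + r)/2, which is below 1 for every r below 1.

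| r | Change variance | ANCOVA variance | Ratio |
|---|---|---|---|
| 0.3 | 1.40 | 0.91 | 0.65 |
| 0.4 | 1.20 | 0.84 | 0.70 |
| 0.5 | 1.00 | 0.75 | 0.75 |
| 0.6 | 0.80 | 0.64 | 0.80 |

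**Step 3. Power at 94 per arm, two-sided 5%.**
- Pairwise: noncentral t with noncentrality 0.35 / √(variance × 2/94). At r = 0.5 this is 0.35 / √(1.00 × 2/94) = 2.40 for change scores and 0.35 / √(0.75 × 2/94) = 2.77 for ANCOVA.
- Overall test: noncentral F with 2 and 279 degrees of freedom and noncentrality 94 × Σ(mean − grand mean)² / variance. For means 0, 0.35, 0.35 and r = 0.5 this is 7.68 for change scores and 10.24 for ANCOVA.
- The single degree of freedom spent on the covariate is ignored.

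| r | Pairwise, change | Pairwise, ANCOVA | Overall F, change | Overall F, ANCOVA |
|---|---|---|---|---|
| 0.3 | 52% | 71% | 54% | 74% |
| 0.4 | 59% | 74% | 61% | 77% |
| 0.5 | 67% | 79% | 69% | 82% |
| 0.6 | 76% | 85% | 79% | 88% |

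The overall F columns assume that both telecare arms work. The pairwise columns carry no multiplicity correction. At a 2.5% level for each contrast, the strictest step of Holm with two contrasts, pairwise ANCOVA power is 60%, 64%, 70% and 77%.

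**Step 4. If 0.35 is in SDs of change instead.** At 100 per arm (normal approximation), pairwise power on change scores is 70% whatever r is. With ANCOVA it is 87%, 82% and 77% at r = 0.3, 0.5 and 0.7. The order is the same.

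**The case against.** **Detail may sit elsewhere.** Contrasts, covariates and test order are often left to a full protocol or analysis plan, and neither is shown. The article also describes the trial as exploratory, and that it is an overall test is inferred from the wording. Lack of detail alone would indeed be no finding. What stands is that the article does name a test for the primary outcome, and that test does not match the aim it publishes.

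**Stronger conclusions a reader might draw, which the documents do not support:**
- *Baseline adjustment makes good a known power shortfall at no cost.* The article does not say which contrast was powered, and 100 per arm is consistent with a one-sided pairwise or a two-sided pooled comparison. How much power is regained depends on r, which is not given. Under a two-sided pairwise reading at 94 per arm, ANCOVA reaches 80% only from r of about 0.52.
- *The plan inflates the error rate to 9–12%.* Those figures (9% for two comparisons with control, 12% for all three pairs) belong to unprotected pairwise tests, which the article does not announce. With exactly three arms, pairwise tests made only after a significant overall F keep the family-wise error at 5%.
- *The plan throws the baseline score away.* Change scores do use baseline, only less efficiently.
- *Controls lack a baseline score because their questionnaire is completed only at 6 months.* That sentence contrasts the follow-up times of the arms, and the Baseline Data section covers baseline.
- *A pooled telecare versus control test should come first.* This is a real trade-off. If only one telecare arm works, such a gate has about 30% to 49% power at 94 per arm (ANCOVA, r = 0.3 to 0.7), against 69% for an unadjusted overall F on 6-month scores.

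**Conclusion.** The point holds in a limited form. The one test named for DMSES is, on its plain reading, an overall test of change. It does not isolate the nurse and peer comparisons with routine care, and it is less precise than a baseline-adjusted analysis. Over r = 0.3 to 0.6, ANCOVA adds 19 points of uncorrected pairwise power at the low end (71 − 52) and 9 at the high end (85 − 76). For the overall test the gains are 20 (74 − 54) and 9 (88 − 79).

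The direction does not depend on r, because (1 + r)/2 is below 1 whenever r is. The size does depend on it, and also on two-sided testing, equal variances, 94 completers per arm and an effect in SDs of the score. None of this shows that the trial as a whole is underpowered or that its error rate is uncontrolled.

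**What to change.** In the Trial Analysis section, replace the ANOVA of improvement for the primary outcome with wording such as:

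> DMSES at 6 months will be analysed by ANCOVA with arm as factor and baseline DMSES as covariate. Adjusted differences for nurse versus control and peer versus control will be reported with 95% confidence intervals. They will be tested at two-sided 5%, either only after a significant overall baseline-adjusted F test, or with Holm correction. Nurse versus peer will be reported as an estimate with a 95% confidence interval. The same model will be used for the other questionnaire scores.

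One of the two multiplicity routes should be chosen before the data are seen.

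The cost is analysis wording only. The model needs baseline DMSES in all arms, as does any analysis of improvement. Either multiplicity route gives up some of the uncorrected pairwise power; the Holm figures in the working show how much at its strictest step.

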#### Eligible patients

Patients who have had a recent HbA1c greater than 8.0% and been advised of the need to improve their glycaemic control, with or without a change in prescribed tablet based therapy.

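### The t-tests named for HbA1c, lipids, blood pressure and BMI test change over time within groups, not telecare against routine care, and HbA1c is likely to fall in every arm anyway

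*Protocol article*

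**What the plan says.** Under Trial Analysis, the article says: "For each patient, change in physiological measures from start to 6 months will be calculated", and that this change will be "analysed using t-test for matched groups for both intervention and control groups". Three other statements in that section bear on the point:

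- Analysis of variance is to assess, among other things, "overall significance of improvement across outcome measures".
- "The magnitude of change in both primary and secondary outcome measures will be estimated and the 95% confidence intervals given".
- "Comparison of nurse and peer supporter outcome data, experiences and feedback will be provided".

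The question to be answered is set elsewhere. Experiments Proposed Including End Points gives the hypothesis that "the telecare intervention compared with routine care alone will improve adherence to the change in medication targeted; improve clinical and psychological status". The second item under Aims of the Trial likewise sets nurse and peer telecare against routine care.

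On entry and baseline, the eligible group was initially "Patients who have had a recent HbA1c greater than 8.0" per cent, lowered to 7.4% ten months into the trial. Baseline Data records the "most recent clinical parameters (HbA1c, BP, BMI, total plasma cholesterol" and further measures at recruitment.

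**The concern.** A matched t-test on change has the null hypothesis that the mean change in one group is zero. Random allocation plays no part in it. Applied to the telecare and control groups in turn, it yields separate statements about time trends and none about the difference between arms.

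This matters more than usual here because three features push HbA1c down in every arm, control included:

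- selection on a high recent HbA1c, which produces regression to the mean if that value is also the baseline;
- the change in management recommended to all referred patients (Proposed Telecare Service);
- the contract incentives to lower HbA1c described in the Discussion.

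A report that followed the sentence literally could present as a telecare benefit a fall that routine care also shows. It could also call telecare effective because a telecare arm reached significance and control did not. Neither is a valid treatment comparison.

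**Working it through.** **Plan's own figure.** The article gives no calculation for the physiological tests and no HbA1c mean, SD or repeatability, so there is nothing to reproduce. The size of the problem has to be illustrated under assumptions.

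**Inputs from the article.** Thresholds 8.0% and 7.4% (Inclusion/Exclusion Criteria). Sample Size gives 125 per arm and 25% attrition: 125 × 0.75 = 93.75, taken as 94 per arm. (The stated evaluable minimum is 100.)

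**Assumed.** HbA1c in the source practices is normal with mean 7.2 to 7.8% and SD 1.3 to 1.5; the correlation r between qualifying and 6-month values is 0.7 to 0.9; the qualifying value is the baseline; nothing truly changes in any arm.

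**Formulas.** With z = (threshold − mean)/SD and λ = φ(z)/(1 − Φ(z)):

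- expected fall = (1 − r) × SD × λ
- variance of the baseline after selection = SD² × (1 + zλ − λ²)
- SD of change = √[(1 − r)² × that variance + SD² × (1 − r²)]
- p = chance that a two-sided 5% paired t-test with n = 94 is significant for a fall
- chance that control is not significant while at least one of two telecare arms is = (1 − p) × [1 − (1 − p)²]

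**Worked example** (threshold 8.0, mean 7.5, SD 1.5, r = 0.8):

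- z = 0.333 and λ = 1.021
- fall = 0.2 × 1.5 × 1.021 = 0.31 points
- variance after selection = 2.25 × (1 + 0.340 − 1.043) = 0.67
- SD of change = √(0.04 × 0.67 + 2.25 × 0.36) = 0.91
- noncentrality = (0.306/0.915) × √94 = 3.25, so p is about 0.90
- discordant pattern = 0.105 × (1 − 0.105²), about 10%

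**Over the assumed range:**

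| Threshold | Spurious fall (points) | Arms with a significant paired test | Control not significant, telecare significant |
|---|---|---|---|
| 8.0% | 0.12 to 0.52 | about 49% to 99% | about 0% to 38% |
| 7.4% | 0.08 to 0.40 | about 27% to 94% | about 6% to 38% |

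The nominal rate for a significant fall is 2.5%. The discordant pattern peaks at about 38%, when p is near 0.42, and shrinks towards zero as p approaches 1, because control then becomes significant too.

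**Check by simulation** (3 arms of 100, 3,000 replicates, no effect in any arm; source mean/SD 7.0/1.2 or 7.5/1.5, r from 0.6 to 0.95). Paired tests were significant in 36% to 100% of arms at 8.0% and 22% to 100% at 7.4%. Comparing the same change scores between arms kept the error at 4.4% to 5.7%, by two-sample t-test or three-arm analysis of variance. So the fault lies in the within-group test; the change score itself is not the cause.

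**The case against.** The strongest reply is that the article does plan a between-arm analysis. The Trial Analysis section speaks of three groups and names analysis of variance for improvement across outcome measures. If the factor is arm and the clinical outcomes are included, the paired tests are supplementary. A reader might infer from the t-test sentence that no between-arm comparison is planned and that randomisation is wasted for these outcomes; the article does not support going that far. But the factor and the outcomes are unstated, physiological measures get their own sentence and their own test, the confidence intervals are for magnitude of change, and the nurse-peer comparison leaves out control. The analysis of variance therefore does not clearly fill the gap. Nor is this a detail left to a fuller plan, because the article names a specific test that does not answer the question.

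Some other replies also stand:

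- Only HbA1c is a selection variable. For blood pressure, lipids and BMI the problem is the missing between-arm test together with shared trends, not regression to the mean from selection.
- The article does not establish that the qualifying HbA1c is the baseline. Baseline Data and the amended criterion point that way, but Clinical Data, which has baseline collected before randomisation and blood specimens taken locally, leaves room for a fresh sample. That would remove much of the selection effect.
- The outcomes are secondary. The article calls the trial exploratory, and the third aim uses clinical data to judge whether a full-scale trial is worthwhile.
- ANCOVA is not required for validity; a between-arm comparison of change is also valid.

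**Conclusion.** The point holds for the physiological secondary outcomes. The test named for them cannot address telecare compared with routine care, and no other sentence in the section clearly does so. For HbA1c, a significant within-group fall is likely even if telecare does nothing: about 49% to 99% of arms at the 8.0% threshold and 27% to 94% at 7.4%, from regression to the mean alone. Reading the paired tests side by side gives a false signal for telecare in about 0% to 38% of null trials. The figures rest on an assumed HbA1c distribution and repeatability and on the qualifying value being the baseline; with very high repeatability or a fresh baseline sample the selection effect is small. The advised change in management and the contract incentives would add to a fall in every arm and are not in these figures.

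A reader might extend the criticism to the primary outcome. The sentence covers physiological measures only, and self-efficacy is outside it. Severity is moderate.

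**What to change.** Do not use the matched-groups t-tests as tests of effect. For each physiological outcome, regress the 6-month value on randomised arm with the baseline value as covariate (ANCOVA). Report the telecare-control, nurse-control and peer-control differences with 95% confidence intervals. A between-arm comparison of change would also be valid but less precise. Give within-arm changes as descriptive means without p-values. If the analysis of variance was meant as the between-arm test, say so by naming its factor and outcomes. State also whether the baseline HbA1c is the qualifying value or a new sample.

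The cost is analysis wording only: baseline and 6-month clinical data are already collected in all arms.

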### Qualitative studies

Several qualitative studies are being conducted in parallel with the main RCT:

1. Telecare supporters' experience: telephone semi-structured interviews with the supporters (diabetes specialist nurses and peer supporters) will be conducted one-year into the intervention. The interviews will aim to capture their experience of delivering the intervention, and the impact of helping others on their own physical and psychological well-being (as well as their professional practice, for nurses).

2. Patient experience: telephone semi-structured interviews will be undertaken with a purposive sample of patients allocated to each intervention arm of the trial, to include patients who have improved HbA1c from baseline to 6 months together with others who have failed to improve. The interview will explore participants' views about the service, issues around the provider (e.g. credibility, trustworthiness, helpfulness), elements of the intervention, and benefits of the service.

3. Referring healthcare professional experience: telephone semi-structured interviews will be conducted with twelve GPs and practice nurses following completion of the six-month data collection, in order to capture their views on self-management, experience of patient recruitment and participation in the research study.

The interviews will be recorded and transcribed verbatim. A thematic framework approach will be used to analyse the data [28]. The framework approach is a systematic process of analysing the data, following a clear procedure and allowing the material to be categorised according to key themes. First, in the familiarisation stage, a relevant sample of tapes will be listened to, the transcripts will be read, and notes will be made on key issues and recurrent themes. In the second stage, the notes will be used to set up a thematic framework, based on a priori issues (the interview topic guide), as well as recurring views and emergent issues raised by the participants. In the third stage, the index will be applied to all interview transcriptions, followed by the fourth stage, where data will be rearranged according to themes (process known as charting). In a final stage, data will be mapped and interpreted. The data will be analysed independently by 2 researchers. Where disagreement occurs, consensus will be reached through discussion.

## Discussion

### The Value of the Research to Public Health and Patient Care

It is anticipated that the provision of motivational telecare support will enhance the self-management of patients with type 2 diabetes leading to improved clinical and psychological outcomes and reduction in the likelihood of diabetic complications. In addition to the improvement in individual patient care, the service could provide a cost effective adjunct to routine care, alleviating the resource pressures currently experienced within primary care and secondary care practice while establishing a successful and robust method of responding to the increasing prevalence of diabetes.

The project, in light of its focus upon self-management, peer involvement and telephone support has the potential to demonstrate an approach that is relevant to realising progress towards the achievement of the care targets in relation to not only diabetes, but a range of long term conditions. The intervention offers a valuable tool in dealing with the difficulties and complications of long term conditions, and as such might be applicable in a wide range of settings.

The main trial started in autumn 2004, shortly after the introduction of the new General Medical Services contract for general practice and the implementation of the Quality and Outcomes framework (QOF) [29]. The new GMS contract substantially increased the workload for general practitioners, making participation in research less attractive, and this has had an adverse impact on patient recruitment. However, the QOF targets resulted in considerably more data on diabetes care being routinely collected by GPs for the annual QOF reports, and at the same time the QOF introduce financial incentives to bring the patients' HbA1c levels below the 7.4% threshold through the more aggressive prescription of oral hypoglycaemic agents and insulin. Together, this resulted in slow participant recruitment for the trial, due to a reduction in the number of eligible patients. In response, the clinical threshold for trial inclusion was lowered to allow patients with baseline HbA1c > 7.4% (as opposed to the previous criteria of HbA1c > 8%) to become eligible for telecare, in line with the manner in which practices are organising and delivering their care. The change in protocol mid-way through the trial will have implications on the presentation of the consort diagram and the interpretation of the study's findings.

The qualitative studies conducted in parallel with the main trial aim to capture the views of patients, supporters and health care professionals on their involvement in the study, satisfaction and benefits derived. It will enrich the interpretation of the quantitative data obtained from the main trial, by shedding light on the importance of various components of this complex intervention. Together with the quality assurance procedures, the qualitative studies will help to inform future intervention delivery research, particularly in the areas of patient and peer supporter recruitment, training delivery, the use of the theoretical framework within the intervention delivery, and the experience and potential benefits of telephone support for both patients and the supporters.
